**TNCC**

The plots below show the bottom end of the 95% CI around a VE of 60% and 90% when there are 4 controls per case (i.e. for TNCC 20% are positive and 80% negative) for various coverage figures. (~20% positivity November 2020)

A: 60% VE

[figure not shown]

B: 90% VE

[figure not shown]

**3.11 Laboratory methods**

**Sentinel specimen collection**

For sentinel swabs individuals (or GPs) take combined throat and nose swabs which are sent by post to the PHE Respiratory Virus Unit at Colindale, North London together with a questionnaire. Pillar testing swabs are taken by individuals or staff at testing site and are tested at multiple labs throughout the country.

**Sentinel testing**

Sentinel samples undergo a molecular analysis for circulating influenza A viruses, influenza B viruses, respiratory syncytial viruses A and B, human metapneumoviruses A and B and other coronaviruses in addition to SARS-CoV-2. Laboratory confirmation is undertaken using RT-PCR assays.

**Other tests used**

A positive SARS-CoV-2 test recorded in GP systems may include results of PCR tests from any laboratory and reported lateral flow test results

**3.12 Statistical analysis**

**Study population characteristics by vaccination status:**

Descriptive statistics will be produced on demographic variables and vaccination status within clinical risk groups.

**Cohort study**

V/E is calculated as 1- RR, where RR is the attack rate of the vaccinated group over the attack rate of the unvaccinated group.

Multivariable Poisson regression will be used with vaccination and week set as time varying covariates and all other variables set according to the individual’s status as of 1^st^ September 2022 (or 2023).

Adjustment for week of swab, age group, sex, risk-status and region (or practice) and will be included at minimum. Inclusion of additional variables including consultation quartile, IMD quintile, ethnicity, smoking status, influenza vaccination status, EFI, large residence, Cambridge Mortality Measure, will be considered individually; variables that do not impact both hospitalisation or death VE by more than 1% need not be included (i.e. the same adjustments will be made for both death and hospitalisation VE).

Vaccination status will be a time-varying categorical variable: 0-13 days post dose, 14-90 days post dose, 91-182 days post dose, with separate categories for vaccine type (and manufacturer if required). Vaccinated 6months+ ago will be the baseline category, to look at the incremental benefit of a new dose.

Person time will be calculated in days and adjusted for as an offset in the model.

The reshape and collapse commands in Stata will be used to aggregate person time and events across the levels of the time varying and fixed covariates.

Cohort analyses will be carried out for both hospitalisation and death outcomes.

Primary cohort analysis will include complete cases only, but unknown categories may be included for some missing data items.

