**3.2 Study population and data source**

| Study population to be included:  Cohort study: Approx. 18,800,000 registered persons in England. About 20% of the study population are ≥65 years.  Swab based TND study: Restricting to those consulting their GP with symptoms and swabbed via the sentinel scheme, available positive cases and negative controls will depend on current prevalence and swab rates.  Spring 2023 boosters, will restrict to: individuals aged 75+, immunosuppressed individuals aged 16+  Autumn 2022/2023 boosters, will restrict to: individuals aged 50-74, individuals aged 75+, individuals aged 16+ in clinical risk groups |
| --- |

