**TND study**

V/E is calculated as 1-OR. Where OR is the odds of vaccination in cases compared to controls (SARS-CoV-2 negative).

Multivariable logistic regression will be used with adjustment for week of swab, age group, risk-status and region (or practice), at minimum. Inclusion of additional variables including sex, consultation quartile, ethnicity, IMD quintile, smoking status, EFI, large residence, Cambridge Morality Measure, and indication for swabbing (grouped as ILI / COVID-like illness, ARI or exacerbation) will be considered individually; variables that do not impact VE by more than 1% need not be included.

Vaccination status will be a categorical variable, captured at the time of swabbing: 0-13 days post dose, 14-91 days post dose, 92-182 days post dose, with separate categories for each vaccine type (or manufacturer if required). Vaccinated 6months+ ago will be the baseline category, to look at the incremental benefit of a new dose.

Primary TND analysis will impute onset status (within/beyond 10 days) where this is not given.

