**Flu TNCC**

For analysis of this test-negative case-control study, logistic regression will be used to calculate the unadjusted odds ratios for influenza vaccination in cases compared to controls, with a 95% confidence interval. This will be used to calculate an unadjusted VE as unadjusted VE=1-OR.

Logistic regression will be used to calculate the odds ratio for vaccination, adjusted for week of swab, scheme and age group, and additionally for relevant characteristics which change the vaccine effect by ≥1% (including risk status and sex). This will be used to calculate the adjusted VE. This will be undertaken for all cases/controls in the elderly, working-age adults and children separately, and in relevant subgroup analyses.

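### The cohort's 1% change-in-VE rule judges each further confounder on its own, with no check on what the omitted ones do together; a cumulative comparison with the fully adjusted model is a cheap improvement

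*Protocol*

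**What the plan says.** Study 1, section 3.12, Cohort study, fixes a minimum model: "Adjustment for week of swab, age group, sex, risk-status and region (or practice) and will be included at minimum". Eight candidates remain: "consultation quartile, IMD quintile, ethnicity, smoking status, influenza vaccination status, EFI, large residence, Cambridge Mortality Measure". These "will be considered individually; variables that do not impact both hospitalisation or death VE by more than 1% need not be included". The same adjustments are then used for both outcomes.

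The TND paragraph of the same section repeats the rule for nine candidates: "sex, consultation quartile, ethnicity, IMD quintile, smoking status, EFI, large residence, Cambridge Morality Measure, and indication for swabbing". These "will be considered individually; variables that do not impact VE by more than 1% need not be included".

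Neither paragraph compares the reduced model with one containing every candidate. Neither says whether 1% is a percentage point of VE or 1% of the VE estimate.

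**The concern.** The rule looks only at the shift in VE when one variable is added to the minimum model. A set of variables can therefore each count as negligible and all be left out, although adding them together would move VE by several times the stated tolerance. The omission is avoidable, because every candidate is already collected (Table 1 of Study 1) and the cohort holds about 18.8 million registered persons, so precision gives little reason to drop them.

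Several candidates (smoking, the frailty index, the mortality measure, consultation frequency) are also the nearest measured proxies for the healthy-vaccinee bias that section 4.5 names as hard to capture. If they act in one direction, a narrow cohort interval could be centred on a VE that is off by a few points.

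**Working it through.** The plan gives no figure for how the rule performs, so there is none to reproduce. The inputs from the protocol are the one-at-a-time wording, the 1% threshold and the eight cohort candidates. The rest are assumptions: true VE 40% (RR 0.60), and k independent binary confounders, each with outcome rate ratio 1.3 and prevalence 28% in boosted and 33% in unboosted person-time.

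**1. Bias factor per omitted confounder**

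b = [1 + 0.28 × (1.3 − 1)] / [1 + 0.33 × (1.3 − 1)] = 1.084 / 1.099 = 0.98635.

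**2. Single and joint shifts**

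With k confounders omitted, the minimum-model RR is 0.60 × b^k.
- Joint bias in VE = 0.60 × (1 − b^k).
- Shift seen when one variable is added alone = 0.60 × b^(k−1) × (1 − b).

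| k | b^k | Minimum-model VE | Shift from one variable (points) | Joint bias (points) |
|---|---|---|---|---|
| 1 | 0.9864 | 40.8% | 0.82 | 0.8 |
| 4 | 0.9465 | 43.2% | 0.79 | 3.2 |
| 6 | 0.9209 | 44.7% | 0.76 | 4.7 |
| 8 | 0.8959 | 46.2% | 0.74 | 6.2 |

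Read as percentage points, every variable falls below the threshold and all may be left out.

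**3. Correlated confounders**

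Take eight equicorrelated normal confounders in a log-linear model that lower VE, at true VE 60%. Each is set to move VE by 0.99 points when added alone. The joint shift is then 7.4 points at correlation 0, 3.2 at 0.2, 2.5 at 0.3 and 1.7 at 0.5. At true VE 40% the values at 0.2 and 0.5 are almost the same (3.2 and 1.7).

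**4. Relative reading of 1%**

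In the example above, one variable's shift is 0.79/43.2 = 1.8% of the VE for k = 4 and 0.74/46.2 = 1.6% for k = 8. On this reading all would be kept. Now let eight variables each sit just under the relative threshold (0.99% of a minimum-model VE of 43.5%, or 0.43 points). The per-variable factor is 0.99242 and the joint bias is 0.60 × (1 − 0.99242^8) = 3.5 points.

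**5. Interval coverage at 3.2 points of bias**

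The observed RR is 0.568, so the log bias is ln(0.568/0.60) = −0.0548. Assume equal person-time in the two groups and D events in total. The events then split as D × 0.568/1.568 and D × 1/1.568, and SE = √(1/D1 + 1/D0). Coverage = Φ(1.96 − z) − Φ(−1.96 − z), with z = 0.0548/SE.

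| D | SE | z | Coverage of nominal 95% CI |
|---|---|---|---|
| 1,000 | 0.0658 | 0.83 | 87% |
| 5,000 | 0.0294 | 1.86 | 54% |
| 20,000 | 0.0147 | 3.73 | 4% |

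The protocol gives no expected number of hospitalisations or deaths (the attack rate in 3.10 is for cases), so D is a range.

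**The case against.** **The rule is permissive.** It says variables need not be included, not that they must be dropped, so the analysts may still fit a full model. That stands, and it is why this is an improvement and not an error. But the protocol does state a selection rule, and that rule lets the joint effect go unseen.

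**The example is favourable to the concern.** It needs independent variables, all acting in one direction and each just under the threshold. Sections 4.4 and 4.5 describe biases in opposite directions: high-risk people vaccinate more, and healthy people vaccinate more. The frailty index, mortality measure, consultation frequency and smoking all reflect health status and are likely to be correlated. Age, sex, risk status, week and region are always adjusted for. All of this stands and lowers the expected size. Even so, 1.7 to 3.2 points exceeds the plan's own tolerance read as percentage points.

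**The coverage loss depends on an unknown event count.** This also stands. Estimates split by vaccine type and time since dose will have fewer events than the total.

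**Stronger readings that a reader might infer**
- *That in a small TND, chance inclusion of unrelated variables damages the estimate.* The protocol does not fix the TND size: "available positive cases and negative controls will depend on current prevalence and swab rates". In simulations with nine noise covariates, at least one usually entered at 500 swabs, yet 95% interval coverage stayed at about 93 to 96%. Standard errors rose by only about 3% at 500 swabs and 0.5% at 1,000. A cumulative backward rule kept noise variables about as often, so this is no ground for changing the rule.
- *That the influenza analysis (Study 2, Flu TNCC) has the same defect.* It adjusts "additionally for relevant characteristics which change the vaccine effect by ≥1% (including risk status and sex") but does not say that variables are judged one at a time, so the joint-omission point cannot be read into it.

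**Conclusion.** The point holds as a cheap improvement, mainly for the cohort. As written, the rule allows a set of individually small confounders to be left out with no check on their sum. Under the stated assumptions the undetected bias is 3.2 points for four variables and 6.2 for eight. More realistic correlation brings eight variables down to roughly 1.7 to 3.2 points, opposing directions cancel, and the relative reading of 1% caps it at about 3.5 points at VE 40%. Whether that matters for interval coverage depends on event numbers the protocol does not give. The documents do not show that the cohort VE will be biased, only that the rule could not reveal it.

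**What to change.** In section 3.12, Cohort study:
- State that 1% means one percentage point of VE.
- Fit the model with all listed covariates for hospitalisation and for death.
- Allow covariates to be dropped only while both VEs stay within one percentage point of the fully adjusted VE, judged cumulatively over everything dropped.
- Report the fully adjusted VE beside the final one.

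In section 3.12, TND study, make the same cumulative comparison once, in the pooled TND with its own covariate list, and carry that set into the strata without reselecting. The cohort's set should not be borrowed. For Autumn 2023, section 3.4 schedules the TND analyses for January and May 2024 and the cohort only after the influenza season. The lists also differ: indication for swabbing appears only in the TND, and influenza vaccination only in the cohort. The Flu TNCC section needs no change on this account.

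The cost is a sentence or two in each of the two paragraphs and one additional full model per outcome. That model will be slow: section 4.7 already allows about 10 working days for these analyses.

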**3.4 Study period**

This proposal relates to an ongoing programme of disease surveillance. Data are collected continuously on a daily basis in England. It includes the diagnoses or problems reported at every consultation. The database can be interrogated in relation to any specific disease or in any defined period. It is assumed that the period of COVID-19 activity will continue throughout 2023 and 2024, this will be monitored through surveillance.

Autumn 2022 booster vaccine doses were offered to all age 50+ plus all members of clinical risk groups age 5+ and health and social care workers, carers or close contacts of the immunosuppressed. Autumn booster doses primarily included bivalent Original/Omicron BA.1 mRNA vaccines (Pfizer-BioNTech, Comirnaty or Moderna, Spikevax). The autumn booster vaccination campaign opened 5 September 2022 and closed 12 February 2023.

Spring 2023 boosters were offered to those age 75+ or those with weakened immune systems, during the period 3 April – 30 June 2023. Vaccines given were primarily either bivalent Original/Omicron BA.4-5 mRNA vaccines (Pfizer-BioNTech, Comirnaty) or monovalent Beta recombinant vaccines (Sanofi-GSK, VidPrevTyn).

From Autumn 2023, a new booster vaccine dose will be offered to all age 50+ plus all members of clinical risk groups age 5+ and health and social care workers, carers or close contacts of the immunosuppressed. Autumn booster doses will include monovalent XBB mRNA vaccines, bivalent Original/Omicron BA.4-5 mRNA vaccines, and monovalent Beta recombinant vaccines, depending on age and availability. The autumn booster vaccination campaign will be ongoing from September 2023.

The data may be examined in any arbitrary period according to interest. At the time of writing, Omicron XBB lineages are dominant, but this could change at any time, and variant may impact vaccine effectiveness. Study periods may be amended to cover variant-dominant periods of infection or according to decision makers needs. Cohort analyses may require censoring at the last date in records where outcomes appear to be well captured.

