**Ascertainment**

Vaccination status, date, manufacturer and type is extracted from the study database (and linked from other sources if necessary).

Individuals will contribute pre-booster person time up to the point of booster vaccination and thereafter assigned to categories based on combinations of time since dose and booster vaccination type

Time since dose:

- pre-booster/unboosted (baseline)
- 0-13 days,
- 14-91 days,
- 92-182 days,
- 183+ days

Type of vaccine:

- mRNA XBB
- mRNA bivalent original/BA.4-5
- recombinant Beta

These categories may be assigned separate factors for different manufacturers, as required.

The following are considered ‘odd’ vaccination histories, to be considered for exclusion:

- Other vaccine types than those listed in section 3.4 above
- Vaccination between 13 February and 3 April 2023 (for Spring 23 booster analysis)
- Vaccination between 31 June and 3 Sept 2023 (for Autumn 23 booster analysis)

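### Sections 3.5 and 3.12 fix different reference groups for COVID-19 vaccine effectiveness, so the comparator behind the VE estimates is not settled

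*Protocol*

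**What the plan says.** **Section 3.5 (Exposure, Ascertainment).** The first time-since-dose level is "pre-booster/unboosted (baseline". On movement between levels it says: "Individuals will contribute pre-booster person time up to the point of booster vaccination and thereafter assigned to categories". Those categories run 0-13, 14-91, 92-182 and 183+ days, so the last is an exposed level of its own.

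**Section 3.12, cohort study.** The model levels are "0-13 days post dose, 14-90 days post dose, 91-182 days post dose, with separate categories for vaccine type". There is no 183+ level. Then: "Vaccinated 6months+ ago will be the baseline category, to look at the incremental benefit of a new dose". The opening VE formula uses another term: "RR is the attack rate of the vaccinated group over the attack rate of the unvaccinated group".

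**Section 3.12, TND study.** The levels are "0-13 days post dose, 14-91 days post dose, 92-182 days post dose", followed by the same baseline sentence as in the cohort paragraph.

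**Vaccine types.** Section 3.4 says of the 2022 campaign: "Autumn booster doses primarily included bivalent Original/Omicron BA.1 mRNA vaccines". The type list in section 3.5 has XBB, Original/BA.4-5 and Beta, but no Original/BA.1.

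**The concern.** VE is defined by its comparator. Section 3.5 asks how boosted people fare against people not yet boosted, whatever the age of their last dose. Section 3.12 asks how recently dosed people fare against people whose last dose is at least six months old. Both are reasonable questions, but they are different ones, and no section reconciles them or names one as primary. An analyst who follows either section departs from the other.

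The objective in section 2.2 most directly affected is VE by time since vaccination. The 183+ day level can be estimated under section 3.5. Under section 3.12, read as written, it cannot, because that time has become the reference.

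**Working it through.** The protocol gives no figure that depends on the choice of reference, so there is nothing of its own to reproduce. The check sets the definitions side by side and then applies the protocol's dates.

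**1. Where each kind of person-time goes**

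| Person-time | Section 3.5 | Section 3.12, read literally |
| --- | --- | --- |
| 183+ days after the evaluated booster | exposed, own level | reference |
| Not boosted, last dose 6+ months ago | reference | reference |
| Not boosted, last dose under 6 months ago | reference | not reference |
| Never vaccinated | reference, if unboosted is meant to include them | no stated place |

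Only the second row agrees.

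**2. Inputs (section 3.4)**

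- Autumn 2022: campaign 5 September 2022 to 12 February 2023 (161 days); evaluation ends 2 April 2023.
- Spring 2023: campaign 3 April to 30 June 2023 (89 days); evaluation 3 April to 3 September 2023 (154 days).
- Autumn 2023: starts on the Monday of the first programme week in September 2023. I assume 4 September 2023, with doses to 31 January 2024. No end of follow-up is given.
- Six months is taken as 183 days, since the exposed levels stop at 182. No uptake curve is given, so even dosing over campaign days is assumed.

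**3. Recipients of the evaluated booster returning to the reference** (dose date + 183 days falls on or before the window end)

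- Autumn 2022: 5 September 2022 + 183 = 7 March 2023, and 1 October 2022 + 183 = 2 April 2023. That is 27 of 161 campaign days (17%). Returned time is 1 + 2 + ... + 27 = 378 units. All post-dose time is 161 × (210 + 50)/2 = 20,930 units. The share is 378/20,930 = 1.8%.
- Spring 2023: the longest possible time since dose is 153 days, so none return.
- Autumn 2023 (assumed dates): the first return is on 5 March 2024.

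| Follow-up ends | Campaign days returned | Share of post-dose time |
| --- | --- | --- |
| 31 January 2024 | 0 of 150 | 0% |
| 31 March 2024 | 27 of 150 (18%) | 378/20,325 = 1.9% |
| 30 April 2024 | 57 of 150 (38%) | 1,653/24,825 = 6.7% |
| 31 May 2024 | 88 of 150 (59%) | 3,916/29,475 = 13% |

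**4. Unboosted people with a recent earlier dose, outside the 6-month reference**

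- Spring 2023 start: 3 April 2023 - 183 = 2 October 2022, so Autumn 2022 doses from 3 October 2022 onward are too recent. That is 133 of 161 campaign days (83%). The last qualify on 12 February + 183 = 14 August 2023. Over the whole window, before any new dose, the share of these recipients' time outside is (133 × 134/2)/(161 × 154) = 8,911/24,794 = 36%.
- Autumn 2023 start: Spring doses are 66 to 154 days old on 4 September 2023, so all are outside. They enter between 3 October and 30 December 2023, after 29 to 117 days (mean 73). The share of time outside is 73/150 = 49% for a window ending 31 January 2024, or 73/271 = 27% for one ending 31 May 2024.
- Autumn 2022 start: cannot be checked, because the dates of the preceding campaign are not given.

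**5. What returners could do to VE (illustration, all inputs assumed)**

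Suppose VE is 60% against people who have not had the evaluated booster, and a fraction f of the reference consists of returners who keep residual protection r. The estimate becomes 1 - 0.40/(1 - f·r).

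| f | r = 10% | r = 30% |
| --- | --- | --- |
| 5% | 59.8% | 59.4% |
| 10% | 59.6% | 58.8% |
| 30% | 58.8% | 56.0% |

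**The case against.** The strongest reply is that section 3.12 gives its purpose as the added benefit of a new dose, and section 3.5 moves people out of pre-booster time at the booster. Read together, the baseline could mean a last earlier dose at least six months ago and no new dose yet. Nobody would then return to the reference. This is sensible and close to the fix below. But section 3.12 does not say it, and it still differs from section 3.5, which counts unboosted people whatever the age of their last dose.

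Several stronger readings are tempting, and the protocol does not support them:

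- **Three rival comparators.** The word unvaccinated sits in a generic VE formula, and the model's baseline is named a few lines later. It is probably shorthand. Two definitions remain in conflict.
- **Cohort and TND use different baselines.** They do not; the sentence is the same in both.
- **Most early Autumn 2023 recipients revert.** Section 3.4 says when the cohort evaluation will be done, not when follow-up ends, and it allows earlier censoring.
- **A large dilution of VE by recently protected people in the 6-month baseline.** That baseline excludes recent doses by construction. Only people 183+ days past the evaluated booster can return.
- **Original/BA.1 is excluded.** Section 3.5 defers to section 3.4 for acceptable types, and 3.4 names it. The type list is merely incomplete.

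It also stands that the exclusion of recently dosed people fades over each window, and that in Autumn 2023 it concerns mainly those offered a Spring dose: people aged 75+ or with weakened immunity.

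**Conclusion.** The contradiction is in the text and needs no assumption: 183+ days after the booster is an exposed level in section 3.5 and has no place but the reference in section 3.12, and unboosted people with a recent earlier dose are treated differently too. The VE estimand is not fixed until one definition is chosen.

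The practical size varies by campaign. Return to the reference is small in Autumn 2022 (about 1.8% of post-dose time), impossible in Spring 2023, and undetermined in Autumn 2023. Exclusion of recently dosed people is heavy at the start of the Spring 2023 window (83% of Autumn 2022 campaign days) and the Autumn 2023 window (all Spring doses), but over a whole window it is a minority of their time, 36% and 27-49%. These shares rest on even dosing and, for Autumn 2023, on assumed dates. The protocol gives no uptake, person-time or residual protection, so the change in VE cannot be calculated.

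**What to change.** Write one campaign-specific definition and use it in section 3.5 and in both parts of section 3.12:

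- Exposure is time since the dose of the campaign being evaluated.
- The reference is eligible people with no dose in that campaign whose last dose was at least 183 days ago.
- Recipients in the campaign stay in the 183+ day level and never return to the reference.
- People not boosted in the campaign whose earlier dose is under 183 days old form a separate category, and never-vaccinated people another.
- The VE formula names this reference instead of the unvaccinated group.
- One set of cut-points replaces 14-90/91-182 (cohort) and 14-91/92-182 (section 3.5 and TND).
- Original/BA.1 mRNA joins the type list in section 3.5 for the Autumn 2022 evaluation.

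The cost is protocol wording and the recoding of one variable. The downside is a smaller reference early in the Spring and Autumn 2023 windows than section 3.5 would give, which eases as earlier doses pass 183 days.
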